## 4 TRIAL DESIGN

A pragmatic implementation feasibility clinical trial of HPV self-sampling. The trial is designed to both test the pathway for implementing self-sampling within the NHS cervical screening programme in England and to estimate the associated increase in uptake and coverage. We anticipate that most GP practices invited will want to take part, however, the final number of GP practices included will depend on the recruitment and response rates of participants (as observed early on in the trial-set up).

Eligible women will be identified and offered self-sampling kits via two different pathways running in parallel:

- (i) **Direct mail-out (systematic offer)** - identified via NHAIS (national screening database) and kit posted to women's recorded home address, and
- (ii) **Opportunistic offer** – identified via electronic GP records and women offered kits when they consult GP primary care for any reason.

All participating GP practices will offer kits via both pathways.

### 4.1 Trial set up

The trial is expected to be adopted onto the NIHR portfolio and will therefore have the support of the North Thames Clinical Research Network (NOCLOR) for identifying and setting up GP practices.

We anticipate that recruiting and setting up a large number of GP practices will be challenging. Therefore, we will take a pragmatic approach and have planned for a phased trial set up period over a target period of 3-6 months.

Given that the logistics required for setting up the opportunistic offer will be substantial (e.g. changes to the electronic patient record software, bespoke training to ensure optimal delivery of the intervention, kit supply) whereas direct mail-out can be easily initiated, it is likely that we will start the mailout almost immediately but stagger the opportunistic offer to align with the timing of activities required for site setup.

#### 4.1.1 Randomisation

If feasible we will randomise the week or month that each GP practice starts the trial (see 18.1 Appendix 1: Randomisation). This is likely only be applied to the start of opportunistic offer (not the mailout). This design is like a form of stepped-wedge cluster randomisation (25) in which more clusters (GP practices) are exposed to an intervention towards the end of the trial than early on. The stepped wedge design helps control for confounding factors (via randomisation) on an intervention which may have an underlying temporal trend. The advantages of using this approach are that it will allow us to assess the impact of offering self-sampling more robustly and make any necessary alterations to the process early on with minimal impact to the majority of the trial sites.

#### 4.1.2 Historical cohort “control” data

Historical (retrospective) data will be collected using a pre-written search of the electronic patient record system at participating GP practices for the 12 month period before the trial start. Women who are at least 6m overdue screening or who reached the 15m anniversary on a census date of 12 months before the trial start (“control” data) will be identified. Of these women, we will assess the proportion that were screened in the following 12 month period. This will be collected at or close to trial start (“entry”) for each GP practice and will allow us to more robustly assess the impact of offering self-sampling.

### 4.2 Active recruitment

Active recruitment at each GP practice is planned for up to 12 months but may be longer or shorter depending on self-sampling uptake rates. Potentially, GP practices may recruit for longer if response rates are lower than expected or if further funds are made available to continue the intervention as part of service improvement (e.g. from NHS commissioners) and an amendment to extend the study recruitment period is approved.

In addition, if we find that the uptake of self-sampling is much lower than expected we may recruit additional GP practices. We will also do outreach at the CCG level to boost GP practice engagement and offering of opportunistic kits.

### **4.3 Clinical Follow up**

After recruitment has ended, we will allow an additional 6 months period for all women who test HPV positive on a self-sample to have had follow-up testing and to collect follow up data (including histology).

Individual participant clinical follow-up length for self-sample screen positives during the current protocol will depend on the point at which they are enrolled and will range from 6-18 months.

### **4.4 Passive/Long term follow up**

Long term coverage will be assessed at 13 months after trial recruitment ends.

Depending on permissions and feasibility, we also plan to collect follow up data for all women who return a self-sample at 3 years and 6 years after the end of active recruitment (last self-sample returned) to provide data that will inform the appropriate screening intervals for self-sampling in the future.

The specific data collection included in this long term follow up is further detailed in section 7.8.

### **4.5 Questionnaire-based sub-study**

A cross-sectional, descriptive questionnaire-based sub-study will be nested within the feasibility trial. The purpose will be to understand more about the women who take up the offer of a self-sampling kit, and about their previous barriers to participation. A short questionnaire will be included in the self-sampling kits which are posted or handed out to women. The focus of the sub-study will be on women who do return a kit, but questionnaires will be mailed/handed to all women as part of the YouScreen kit and we will include a small number of questions designed to understand why some women do not return the kit – albeit anticipating a low response rate in this group. In this brief questionnaire sub-study, we will use the Precaution Adoption Process Model (PAPM) (26) as a theoretical framework and will draw on [name] previous work to explore previous barriers to participation.(27-30)

In the patient information booklet, women will be invited to complete the questionnaire and mail it to KCL by freepost. Questionnaires will be a single page of A4, folded and sealed (self-seal), with pre-paid postage and address printed on the reverse side. We may include a link for women to complete the questionnaire online instead of completing and returning by post.

The questionnaire will be pre-printed with the kit ID number to allow linkage to information about the mode of kit offer, return of self-sample, the woman's cervical screening history, HPV result and (if HPV positive) attendance for follow-up, as well as basic demographic information not collected as part of the questionnaire e.g. LSOA (Lower Layer Super Output Area).

## **5 TRIAL SETTING**

All 212 GP practices in the Clinical Commissioning Groups (CCG) within North East (NEL) and North Central (NCL) London with the lowest cervical screening coverage will be invited to participate. These are:

- Camden (54.6% coverage 2017/18, 33 GP practices, NCL),
- Islington (62.8% coverage 2017/18, 33 GP practices, NCL)
- Barnet (63.0% coverage 2017/18, 57 GP practices, NCL)
- Tower Hamlets (60.9% coverage 2017/18, 36 GP practices, NEL)
- Newham (62.9% coverage 2017/18, 53 GP practices, NEL)

We estimate that approximately 106 (50%) GP practices will be interested in taking part. For IT reasons, only practices using Egton Medical Information Systems (EMIS) will be included. We will set up as many of these 106 practices as possible, depending on time and resources.

## 6 PARTICIPANT ELIGIBILITY CRITERIA

The trial population will comprise women who are registered at a participating GP practice, aged  $\geq 25$  and  $\leq 64$  who are at least 6 months overdue their cervical screening.

### 6.1 Inclusion criteria

A participant will be eligible for the trial if all of the following criteria apply:

- Women  $\geq 25$  and  $\leq 64^*$  years old, and
- Eligible for cervical screening under the NHS CSP in England, and
- At least 6 months overdue cervical screening; and
- Registered at a participating GP practice

A sub-group of eligible women will also be eligible for direct mailout of self-sampling kits (see section 7.2.1). – those who reach the 15-month anniversary of their last test due date without being screened.

\*Women aged 65 will not be targeted but if included will not be considered a protocol violation. This is because although women aged 65+ are not invited to routine cervical screening they may still be offered a test if they have not been screened since age 50, or if they have not yet met the criteria to be ceased from the programme.

### 6.2 Exclusion criteria

A participant will not be eligible for the trial if any of the following criteria apply:

- Women unable to provide informed consent
- Women under the care of colposcopy within the last 36 months and/or due for a test of cure (HPV test to confirm if a woman has been successfully treated after treatment for cervical abnormalities)

#### 6.2.1 Pregnancy

In addition to the eligibility criteria, women who are pregnant will be advised in the participant information booklet to not take part in the trial. There are no safety concerns with pregnant women self-collecting a vaginal swab, however the trial will advise against it for two reasons. The first is that the CE-mark for the Copan 552C.80 FLOQswab does not cover pregnant women because pregnant women were not included in Copan's validation studies. The second is that there are potential issues with ensuring adequate follow up within the trial lifetime if they test HPV positive on a self-sample (colposcopy is less inaccurate due to hormone changes and excisional treatment to the cervix for high grade cervical disease is sometimes deferred until post-partum). The NHSCSP recommend that pregnant women defer cervical screening until 12 weeks post-partum.

It is not practical or feasible to assess whether a woman is pregnant using the NHAIS database therefore some pregnant women may be sent kits in the post.

#### 6.2.2 Women who have formally opted out of cervical screening

For the direct mailout cohort, women who are documented in NHAIS as having formally opted out of cervical screening (by returning a signed cervical screening disclaimer form) will not be sent kits.

However, women who have formally opted out of cervical screening may be offered a kit opportunistically at their GP practice at the discretion of the health professional consulted. This is because women may have opted out of cervical screening because of barriers associated with the pelvic examination and self-sampling may be acceptable to these women (as observed in our previous pilot study)(16).

#### 6.2.3 Women who are HIV positive

Women who are documented as being HIV positive in the Cervical Screening Programme are recalled annually (as opposed to 3 or 5 yearly). These women will only be included in the opportunistic offering of self-sampling. By definition, they will never reach the 15-month anniversary of last test due date to trigger direct mail out of a kit as their Next Test Due Date (NTDD) is reset

every 12 months. HIV status will not be stored or reported to King's College London at any point during the trial.

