Once a valid self-sample result (i.e. either Human papillomavirus self-sample test positive or Human papillomavirus self-sample test negative. Results for unavailable/Insufficient self-sample for human papillomavirus testing will be ignored) has been coded into the electronic GP records the alert will be programmed to switch off. With this trial design, potentially women may receive more than one kit offer, either opportunistically if they consult more than once during the trial period or if they are sent a kit via direct mail-out and are offered self-sampling opportunistically at their GP practice prior to an adequate self-sample result being entered. The rationale for allowing women to be offered kits opportunistically more than once is because in our previous study we found that women who declined kits accepted subsequent offers. This could happen for example if women are feeling particularly unwell at the first offer and in better health at the subsequent visit.

The laboratory will have a protocol to ensure that it rejects self-samples if one has already been tested in that screening round (i.e. in the last 3 years if aged 25-49 or the last 5 years if aged 50-64) unless the self-sample recorded was not reportable because it was unavailable or not returned in the acceptable time frame for sample validity.

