## 7.5 Clinical management & NHAIS (call/recall) pathway

NHS Digital will implement the changes required in NHAIS to support self-sampling. A specification outlining the changes required in the system to support the self-sampling pathway has been jointly drafted with input from NHS Digital, the trial team, clinical experts (consultant gynaecologist and GPs on the Joint Steering Group), PHE, Research Advisory Committee (RAC) and HSL laboratory. This includes appropriate failsafe measures for cervical screening self-sampling. **4Error! Reference source not found.** summarises the clinical management for women who return a self-sample in the trial and the associated self-sampling pathway in the national cervical screening database NHAIS (call/recall). Self-sampling will be recorded in NHAIS and will elicit the relevant changes in the call/recall pathway in NHAIS. This will allow us to accurately calculate the impact of self-sampling on coverage and to test the IT pathways. Proposed NHAIS codes for self-sampling are in Table 1.

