### 7.5.1 HPV Negative

Women who test HPV negative on a self-sample will not require any further action or tests. They will have their NTDD reset within the national cervical screening (call/recall) programme according to age (3 years if aged 25-49y, 5y if aged 50-59, or if aged 60 or above at the time of testing, they will be ceased from the cervical screening programme (in keeping with the usual auto-ceasing rules).

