**Table 1 Proposed codes for recording self-samples in NHAIS**

| Self-Sample HPV result             | HPV primary screening flag | Infection Code | Result Code | Action Code | Call/recall Action in NHAIS                                                                                                                                                                                  |
|------------------------------------|----------------------------|----------------|-------------|-------------|--------------------------------------------------------------------------------------------------------------------------------------------------------------------------------------------------------------|
| HPV Negative                       | S                          | 0              | X           | A           | Reset Next Test Due Date (NTDD) using the standard call/recall protocol.                                                                                                                                     |
| HPV Positive                       | S                          | 9              | X           | R (3)       | Reset NTDD with an early recall of 3m (will restart the call/recall cycle and automatically add them to the PNL list that is sent to GPs. NTDD would be reset again if the women had standard screening test |
| HPV unavailable (insufficient DNA) | S                          | U              | X           | H           | NTDD unchanged.                                                                                                                                                                                              |

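### Section 7.5.1 sets recall by age alone after an HPV-negative self-sample, with no exception for the annually recalled HIV-positive women whom section 6.2.3 admits

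*Protocol*

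**What the plan says.** Protocol section 6.2.3 states: "Women who are documented as being HIV positive in the Cervical Screening Programme are recalled annually (as opposed to 3 or 5 yearly". It adds: "These women will only be included in the opportunistic offering of self-sampling". The reason given is that their next test due date is reset every 12 months, so they never reach the 15-month trigger for a posted kit.

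Section 7.5.1 says that women with an HPV-negative self-sample need nothing further, and that their due date is reset within the "programme according to age (3 years if aged 25-49y, 5y if aged 50-59" and, "if aged 60 or above at the time of testing, they will be ceased from the cervical screening programme", in line with the programme's normal rules for automatic ceasing.

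Table 1 has one HPV-negative row, action code A: "Reset Next Test Due Date (NTDD) using the standard call/recall protocol". The HPV-positive row carries its own interval, code R (3): "Reset NTDD with an early recall of 3m".

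**The concern.** The two sections give different recall intervals for the same women. Section 6.2.3 says that 3- or 5-yearly recall does not apply to women documented as HIV positive. Section 7.5.1 gives exactly those intervals to every woman with a negative self-sample. It is the only place in the protocol that states intervals for a negative result.

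At stake is the follow-up of a group that the programme has chosen to recall more often. If the database were programmed from 7.5.1 as it stands, a negative self-sample would lengthen the interval, or at 60 and above end recall altogether. The trial team could not see this in its own data, because 6.2.3 says that HIV status is neither stored by nor reported to it. Getting recall intervals right is also one of the things that section 2 says the trial is there to establish.

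**Working it through.** No figure in the protocol needs reproducing. The check is a comparison of sections, followed by interval arithmetic.

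**Are these women in scope of 7.5.1?** Yes. Section 6.2.3 admits them through the opportunistic offer, and 7.5.1 covers all women who test HPV negative on a self-sample.

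**Is an exception made elsewhere in the text shown?** No. Apart from 6.2.3, HIV appears only in the abbreviation list. Table 1 states a non-routine interval for positive results only. Pregnant women, by contrast, are discussed in 6.2.1 and then given their own management section, 7.5.5.

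**Inputs for the arithmetic.** Annual recall is 12 months (6.2.3). The reset after a negative result is 3 years = 36 months at 25-49, 5 years = 60 months at 50-59, and ceasing from 60 (7.5.1).

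**Formulas.** Delay = interval applied − 12 months. Annual recalls skipped = (interval applied ÷ 12) − 1.

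| Case | Interval applied | Delay | Annual recalls skipped |
|---|---|---|---|
| NHAIS keeps annual recall, any age | 12 months | 12 − 12 = 0 | 12/12 − 1 = 0 |
| 7.5.1 taken literally, age 25-49 | 36 months | 36 − 12 = 24 months | 36/12 − 1 = 2 (months 12, 24) |
| 7.5.1 taken literally, age 50-59 | 60 months | 60 − 12 = 48 months | 60/12 − 1 = 4 (months 12, 24, 36, 48) |

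For women ceased at age *a* from 60 to 64, assume that annual recall would otherwise run to age 64, which the protocol does not state. Recalls lost = 64 − *a*, that is 4, 3, 2, 1 and 0 at ages 60, 61, 62, 63 and 64.

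The first row is the lower bound and the literal readings are the upper bounds. They count invitations, not tests that would have taken place.

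**The case against.** The best defence is that 7.5.1 describes the general case only. It places the reset inside the national programme and ties ceasing to the programme's normal rules. Table 1 defers to the standard protocol and gives no interval of its own, so it is silent rather than contradictory. Section 6.2.3 says what the programme does for women with HIV: it recalls them every year. On that reading NHAIS would simply keep 12 months.

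There are also controls. Section 7.5 refers to a separate NHAIS specification drafted with NHS Digital, clinical experts and the laboratory, and says of it: "This includes appropriate failsafe measures for cervical screening self-sampling". Section 12.1.2 names the programming that resets the due date as a main delivery risk and allows time to test it. Section 13.1.1 provides for regular monitoring with NHS Digital and for suspending the recording of self-samples. The specification and Figure 4 are not available here.

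Exposure is narrow as well. The alert in 7.2.2 flags only women with no test recorded for 3.5 or 5.5 years, the offer is at the professional's discretion, and only negative results matter.

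Most of this stands. It means that an operational error cannot be claimed. It does not reconcile the two sections. If NHAIS keeps 12 months, 7.5.1 misdescribes what happens to these women. If NHAIS follows 7.5.1, their recall is wrong. None of the controls, as described, mentions this case.

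A reader might also infer from the laboratory's repeat-sample rule in 7.2.2, which goes by age, that a self-sample sent a year later would be refused. That adds nothing here. The rule sets no recall date. Active recruitment is planned to end by 12 months (7.10) and the laboratory stops one month after the last kit (7.6.3.2), so an annual repeat would hardly arise.

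**Conclusion.** The point holds as a defect of wording with a possible safety consequence. Section 7.5.1 is wrong as written for women on annual recall, and Table 1 does not correct it. The size runs from no change, if NHAIS keeps annual recall, to a delay of 24 months (2 recalls skipped) at 25-49 or 48 months (4 skipped) at 50-59. From 60, recall would end, with up to 4 recalls lost on the assumption that annual recall runs to 64.

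A reader might infer that HIV-positive women in this trial will be moved to 3- or 5-yearly recall. The documents do not support that, because actual NHAIS behaviour depends on standard rules and a specification that are not shown. Nor do they support any count of women harmed, since no number of HIV-positive women is given. A reader might also suspect an effect on the results. There is none to claim: coverage in section 3.2 is counted from tests and age bands, not from the next recall date, and no sample-size figure uses recall after a negative result.

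Severity is minor. It is worth correcting because it concerns patient safety and the wording change costs almost nothing.

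**What to change.** Add one sentence to 7.5.1 and a matching note to the HPV-negative row of Table 1: women on annual recall keep a 12-month next test due date after an HPV-negative self-sample and are not automatically ceased on age alone. A cross-reference to 6.2.3 would help.

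Include this case in the NHAIS specification described in 7.5 and in the testing before the trial starts described in 12.1.2, with a test record on annual recall in each age band, including 60 and above.

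The cost is two sentences and one added test case, with no change to endpoints, sample size or analysis. If testing showed that NHAIS does not keep annual recall after a self-sample, reprogramming would be needed. That would cost more, since 12.1.2 already treats this programming as a main delivery risk, which is a reason to check it early.

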#### **6.2.4 Women who have opted out of NHS data usage via the National Opt-Out**

The national data opt-out was introduced on 25 May 2018 enabling patients to opt out of the use of their data for research or planning purposes. Women who have opted out of their NHS data usage via the national opt-out will be excluded from the study.

- For the mailout cohort, women who are documented in NHAIS to have formally opted out via the national opt-out will be removed from the data extract before the kits are posted.

